## Abstract

**Background:**

Reduction in neonatal deaths has been a major challenge globally. To prevent neonatal deaths, improvements in newborn care have been promoted worldwide. The World Health Organization Western Pacific Regional Office has been promoting the Early Essential Newborn Care (EENC), a package of specific simple and cost-effective interventions, in their region. However, mere introduction of EENC cannot reduce neonatal deaths unless quality of care is ensured. In Lao PDR, the government introduced self-managed continuous monitoring as a sustainable way to improve the quality of care described in the EENC.

**Methods:**

A clustered randomized controlled trial was designed to compare the effectiveness of self-managed continuous monitoring with external supervisory visits to monitor health workers’ satisfactory EENC performance and their knowledge and skills related to the EENC in Lao PDR. Determinants of EENC performance will be measured with a structured questionnaire developed based on the Theory of Planned Behaviour, which predicts future behaviour. During self-managed continuous monitoring activities, health workers in each district hospital will conduct periodical peer reviews and feedback sessions.

Fifteen district hospitals will be randomly allocated into the self-managed continuous monitoring (intervention) and the supervision (control) groups. Fifteen health workers routinely involved in maternity and newborn care including physicians, midwives and other health staff will be recruited from each hospital (effect size 0.6, intra-cluster correlation coefficient 0.06, 5% alpha error and 80% power). We will compare the change in the mean score of the determinants before and one year after randomisation between the two groups. We will also compare the retention of knowledge and skills related to the EENC between the two groups. The expected enrolment period is July 20th, 2017 to July 20th, 2018.

**Discussion:**

This is the first cluster randomized trial to evaluate a self-managed continuous monitoring system for quality maintenance of newborn care in a resource-limited country. This research is conducted in collaboration with the Ministry of Health and international organizations; therefore, if effective, this intervention would be applied in larger areas of the country and the region.

**Trial registration:**

This trial was registered at UMIN-CTR on 15th of June, 2017. Registration number is UMIN000027794.

**Electronic supplementary material:**

The online version of this article (10.1186/s12913-018-3311-7) contains supplementary material, which is available to authorized users.

## Background

While the mortality rate for children under the age of five years has almost halved in the last 20 years globally, the neonatal mortality rate has not had such a dramatic reduction. In fact, the proportion of under-five child deaths due to neonatal mortality has increased worldwide [1, 2]. Approximately 7000 neonates died per day in 2015 mainly due to prematurity, birth-related complications (birth asphyxia) and neonatal sepsis [2]. In the Western Pacific Region, more than 70% of child deaths are due to neonatal complications, and one neonate dies every two minutes [3, 4]. Given that complications in the first month of life have become the leading cause of death in children under five, actions to improve neonatal health have become tremendously important to achieve Sustainable Development Goal 3 in 2030 [5]. Simple methods can be applied to prevent neonatal deaths and complications due to preventable factors within the first 24 h of birth, during which about half of all neonatal deaths occur [3, 6, 7].

Essential Newborn Care (ENC) is an evidence-based and effective measure to prevent newborn deaths and is recommended globally [8–11]. Helping Baby Breathe and the Neonatal Resuscitation Program are wide-spread educational programs that provide training materials for health care providers that focus on improvements in neonatal resuscitation in addition to providing information on essential skills [8]. Early Essential Newborn Care (EENC) aims to prevent early neonatal deaths by changing routinely implemented harmful practices through coaching involving a set of specific simple actions in birth assistance. The EENC does not require special medical equipment or medications and can be implemented in resource-limited countries. It is an officially recognised program by the World Health Organization (WHO) and the United Nations Children’s Fund (UNICEF) and is distinguished from ENC. The scale up of EENC activities is led by the Western Pacific Regional Office (WPRO) of the WHO, and 27,000 health workers in over 2000 facilities have been trained under this program in 8 prioritised countries in the region [9, 10]. It is estimated that at least 50,000 neonatal deaths could be averted by applying the EENC each year in the Western Pacific Region [9].

Lao People’s Democratic Republic (Lao PDR) had the highest neonatal mortality rate (27.2 neonatal deaths per 1000 live births in 2012) in the WHO Western Pacific Region [3, 9]. In 2015, adopting the EENC in Lao PDR to accelerate the reduction in neonatal deaths was therefore seen as a priority. The country is divided into 18 provinces, which are themselves divided into smaller districts. The Lao PDR health facilities are composed of central hospitals in the Vientiane capital, provincial hospitals in each province capital and district hospitals. The EENC was introduced in central hospitals and then expanded to 17 of the 18 provinces in 2016. The government committed to a plan of rolling out the EENC to district hospitals in 2017.

Along with the expansion of the program, retention of knowledge and practical performance have become issues of interest to provide quality in EENC, especially at the district level. Previous studies showed that neonatal resuscitation training improved participants’ knowledge, skills and performance; however the long-term effect of such training on the retention of knowledge, skills and performance remains uncertain [11–13]. Another study suggested that training improved the level of knowledge and skills but did not change daily practice [14]. These studies suggested that different mechanisms to maintain skills, knowledge and performance of EENC for a prolonged period after training would be necessary. The introduction of EENC can only be effective in reducing neonatal deaths long-term if routine EENC of high quality is maintained. Health workers’ competency is known to be critical for service quality [15]. Core competencies for midwifery care have been defined by the International Confederation of Midwifes as the demonstration by health workers of knowledge, skills and appropriate behaviour [16].

Although an external supervisory visit is a common method to promote behavioural changes among health workers and to maintain quality of care in many countries, it is not feasible in resource-limited settings due to budgetary and human resource demands. Furthermore, systematic reviews examining the use of supervision as a method to improve quality of care in low- and middle-income countries reported mixed evidence of the effect of supervision on quality improvement [17–19]. In Lao PDR, there is only a limited capacity to implement routine supervision. In addition, efforts made by district hospitals to solve problems after the supervisory visits are insufficient and, eventually, problems remain unsolved [20].

Self-managed continuous monitoring requires a lower budget and is considered more feasible than external supervisory visits. To build a sustainable system for continuous quality improvement, self-managed continuous monitoring was introduced in Lao PDR with support from the WHO. Self-managed continuous monitoring is expected to improve health workers’ knowledge and technical skills and to promote daily EENC practice [21]. However, little is known about the effectiveness of self-managed continuous monitoring on quality of care compared to that of external supervisory visits.

### Study objectives

This study aims to test whether in Lao PDR, a resource-limited country, self-managed continuous monitoring of activities for the EENC conducted by health workers involved in maternity and newborn care in district hospitals improves health workers’ behaviour (routine performance of standardised EENC) as well as retention of knowledge and skills after the EENC coaching. We have set determinants of EENC performance as a primary outcome because previous studies have pointed out that changing behaviour of health workers is difficult but key to providing appropriate care for patients. The determinants are factors that can predict future performance of EENC. We have selected Lao PDR because it has been a prioritised country in the Western Pacific Region and EENC has been strongly promoted in that country.

The specific objectives of this cluster randomized trial are:To test whether self-managed continuous monitoring is effective in changing determinants of EENC performance amongst health workers at the district level compared with supervision.To test whether self-managed continuous monitoring is effective in improving retention of technical knowledge and skills for EENC amongst health workers at the district level compared with supervision.To specify the EENC components for which self-managed continuous monitoring is most effective for retaining knowledge and skills.To evaluate whether self-managed continuous monitoring improves the environment required to enable EENC implementation in district hospitals. An enabling environment is one with policy commitment, availability of commodities and equipment and human resources in district hospitals.

We expect that our findings will inform decision makers on the effectiveness of the self-managed continuous monitoring model at the district level and provide them with useful information to then design an effective monitoring system. We trust the lessons learnt from Lao PDR to be applicable to other resource-limited countries.

## Methods/design

### Trial design

This study is a cluster randomized controlled trial with four strata based on province and history of attendance for EENC coaching. It aims to evaluate superiority of self-managed continuous monitoring over supervision. It is a two-armed parallel group study. Allocation ratio is 1:1 within the same stratum.

### Study setting

This study targets district hospitals in Xiengkhuang and Huaphanh provinces of Lao PDR. The level of maternal and child health coverage of these two provinces corresponds to the national average [22], and the government usually selects these two provinces to test new interventions.

The clusters, or district hospitals, will be divided into four strata by location (Xiengkhuang or Huaphanh) and by history of attendance of EENC coaching. Clusters will then be chosen from each of the strata. We will evaluate the overall effects of the intervention on the outcome but will not conduct stratified analyses.

Of note, the two provinces are different in several aspects such as road conditions, culture and economic status. Huaphanh province has a larger number of poor and remote villages, and health outcomes in this province are worse than in Xiengkhuang [22, 23]. Indeed, capacity of health staff is said to be higher and medical facilities better equipped in Xiengkhuang [24, 25]. To remove the effect of these differences between the two provinces, the clusters are divided by province.

Two district hospitals in each province received EENC coaching in 2016. The other district hospitals will receive EENC coaching upon entry into this study. Within one and a half days, the EENC coaching provides information on the theoretical rationale for EENC and teaches health workers EENC technical skills. Given that district hospitals that have already received EENC coaching might have different levels of determinants of EENC performance, knowledge and skills compared to districts that have not, the district hospitals will be divided based on a history of attendance to receive EENC coaching.

This study is led by the Teikyo University Graduate School of Public health in collaboration with the Lao Ministry of Health (MoH) and the WHO. The MoH has reviewed and agreed on the study protocol. Although the research team will mainly lead this study, the MoH will be responsible for conducting the EENC coaching and supervision in district hospitals. MoH will also be involved in incorporating the study results into the country’s policy.

### Participants and eligibility criteria

#### Inclusion criteria

Health workers who are routinely involved in maternal and newborn care and have received EENC coaching in the target district hospitals are eligible to join this study. Health workers include obstetricians, paediatricians, midwives, nurses and other types of health workers. The eligible participants need to provide written informed consent.

#### Exclusion criteria

To minimise loss to follow up, we will exclude those who are scheduled to leave their current workplace or retire within one year.

### Recruitment and allocation

#### Recruitment

After identifying eligible participants, written informed consent will be obtained from each. To obtain sufficient numbers of participants from each district hospital and to minimise loss to follow up, we will involve all district hospital directors. Directors will usually monitor, supervise and encourage their staff in their duties. Getting directors’ participation is therefore critical. Researchers, together with provincial and district staff, will set up a schedule to ensure that all participants are in the district hospital at the time of data collection or supervision. In the intervention group, central and provincial staff will also remind district directors and local staff to conduct self-managed continuous monitoring and submit reports. The expected enrolment period is July 20th, 2017 to July 20th, 2018.

#### Allocation

There will be 6 clusters (district hospitals) in Xiengkhuang and 9 clusters in Huaphanh province. Clusters in each province will be divided into two strata based on history of attendance of EENC coaching, and then will be randomized to two intervention groups (self-managed continuous monitoring and supervisory visits) within each stratum following random allocation rule with urn model. Figure 1 summarizes how district hospitals will be allocated to two intervention groups.

**Fig. 1 Fig1:**
[figure not shown]
Trial flow

#### Blinding

Blinding of participants would be difficult in this study due to the nature of the intervention. We will choose assessors amongst central and provincial officials who do not know about the allocation. Standardised checklists will be used for outcome measurement to minimise bias. Team members who manage data will be blinded until the code is open. Members who analyse data will also be kept blinded.

#### Intervention

##### Intervention group: Self-managed continuous monitoring

Self-managed continuous monitoring is monitoring conducted by the recruited health workers in each district hospital following the Ministry of Health guidelines (Additional file 1). In the self-managed continuous monitoring group, district health workers will form a multi-disciplinary team with representatives from both maternity and paediatrics and the team will hold quarterly feedback meetings to discuss solutions and make action plans based on the results of the periodic peer evaluation of clinical practice and interviews of mothers of neonates. After randomisation, training to introduce self-managed continuous monitoring will be conducted for the intervention group. The peer evaluation and interviews will be conducted at every birth after randomisation. Provincial officials will remind the districts to submit quarterly reports after their self-managed continuous monitoring activities.

##### Control group: Supervisory visit

After randomisation, supervision will be provided every three months to the control group. Members of the Provincial Health Department and/or the Provincial Hospital will visit district hospitals to observe whether district health workers are providing appropriate care through direct observation and/or chart review and whether there are sufficient essential medicines and equipment available using standardised checklists. Provincial supervisors will also interview mothers who gave birth at a hospital to determine whether they have received appropriate care. Provincial supervisors will give feedback to district health workers as needed and ask them to solve any problems that are detected.

### Endpoints

The primary endpoint is the change in determinants of EENC performance amongst health workers. Secondary endpoints are 1) EENC knowledge, 2) EENC skills and 3) hospital environmental changes facilitating implementation of EENC. We will also compare the cost of monitoring activities between the two groups. Measures and schedule of data collection are explained in the next section.

### Participant timeline

Figure 2 shows the trial schedule. After identifying potentially eligible participants, a trained research staff member at the central or provincial level will explain the goals and procedure of the study to them, invite them to participate and obtain written consent from those who desire to participate after the explanation.

**Fig. 2 Fig2:**
[figure not shown]
Trial schedule

District hospitals that have not yet received EENC coaching will receive coaching before randomisation. Pre-coaching evaluation will be done to measure determinants of EENC performance and knowledge related to neonatal care before the introduction of EENC.

After the coaching, the districts will be randomly allocated into two groups. A research team member will distribute and explain a structured questionnaire to be filled out by the district participants to measure determinants of EENC performance and will administer written and simulation tests to measure EENC knowledge and skills. The collected data will be used as baseline data.

District hospitals that are allocated into the intervention group will receive a half day of on-the-job training on self-managed continuous monitoring. A research staff member will explain the concept, schedule, procedure and checklists of self-managed continuous monitoring.

After randomisation, district hospitals in the intervention group will conduct self-managed continuous monitoring and submit quarterly reports to the province. In the control group, provincial supervisors who are not involved in the research will visit districts every three months to supervise implementation of EENC and give feedback to district health workers.

Study participants will be monitored until one year after entry into this study or withdrawal from the study for any reason. The date of the final evaluation will be determined once a schedule for enrolment is set for each district. We will allow a variation of a month around the endpoint for timing of the final evaluation. The outcome data on participants who withdraw from the study before one year will be collected at the time of withdrawal.

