##### Determinants of EENC performance amongst health workers

Determinants of EENC performance by health workers will be quantified by using a structured questionnaire (Additional file 2) that was developed based on the Theory of Planned Behaviour. [27–30] The questionnaire will measure determinants of behaviour: attitude, subjective norms, perceived behaviour controls and behaviour intentions that would influence future behaviour. The higher the total score of the determinants, the higher the likelihood of staff practising EENC in their daily work. Data will be collected six times from both groups during the study period: 1) before EENC coaching, 2) immediately after randomisation, 3) three months after randomisation, 4) six months after randomisation, 5) nine months after randomisation, and 6) one year after randomisation. Provincial officials will remind by telephone each district to fill out their own questionnaire every three months. Administered questionnaires will be saved in each district until provincial supervisors or assessors visit the district, at which point they will collect the questionnaires and submit them to the investigators. In the intervention group, checklists used for the self-managed continuous monitoring and interviews with pregnant women who receive the EENC will be stored and compared with the results of the questionnaire.

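### The self-completed baseline for the primary change score is scheduled after randomisation, with no stated step withholding the allocation until it is complete; the abstract places it before randomisation

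*Protocol article*

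**What the plan says.** All places are in the protocol article.

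- **Order of steps (Participant timeline).** Hospitals not yet coached are coached first; then "After the coaching, the districts will be randomly allocated into two groups". The next step is a "structured questionnaire to be filled out by the district participants to measure determinants of EENC performance", together with the written and simulation tests. Of these results the section says "The collected data will be used as baseline data". The half-day training on self-managed monitoring for the intervention hospitals is described after that.
- **Schedule (Determinants of EENC performance amongst health workers).** The score is collected six times, beginning "1) before EENC coaching, 2) immediately after randomisation, 3) three months after randomisation". The sections on knowledge and skills give their baseline tests the same timing, just after randomisation.
- **Endpoint (Data analysis).** The primary endpoint is the change in the determinants score from baseline to one year after randomisation. It is analysed with a linear mixed model, first crude and then adjusted for baseline and other variables.
- **Blinding.** "Blinding of participants would be difficult in this study due to the nature of the intervention". Assessors are to be officials unaware of the allocation.
- **Abstract, Methods.** "We will compare the change in the mean score of the determinants before and one year after randomisation between the two groups".
- **Length of follow-up (Participant timeline).** "Study participants will be monitored until one year after entry into this study", whereas the outcome sections and Data analysis count the year from randomisation.

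**The concern.** A baseline is safe to subtract or adjust for because the allocation cannot have influenced it. Here the schedule places the baseline after the allocation. The instrument is also one that expectation could move: staff report their own attitudes, perceived norms, perceived control and intentions about EENC. A team that has just heard it will monitor itself, or be visited every three months, may answer differently from one that has heard nothing. Assessor blinding does not protect a form that participants fill in themselves.

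Any difference created this way is carried into the primary estimate. More hospitals would not remove it. Nor would adjusting for the baseline score, because that covariate would itself have been affected by allocation.

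Separately, the abstract names a different baseline time point, so the article does not give one consistent definition of its primary change score.

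**Working it through.** **1. Which score is the baseline?**

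| Source | Baseline implied |
|---|---|
| Participant timeline; Determinants section | After coaching, just after randomisation |
| Data analysis | Baseline to one year after randomisation; baseline not dated |
| Abstract, Methods | Before randomisation |

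The only determinants score scheduled before randomisation is the pre-coaching one. Study setting says two hospitals in each of the two provinces were coached in 2016, so 15 − 4 = 11 hospitals are newly coached. In those 11, the abstract's reading would add the coaching effect to the change, in both arms.

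**2. How a shift at baseline enters the estimate**

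Let s be the shift in mean baseline, intervention minus control, caused by learning the allocation.

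- Unadjusted change score: (I₁ − I₀) − (C₁ − C₀). If I₀ − C₀ moves by s, the estimate moves by −s.
- Outcome adjusted for the baseline score with slope b: the estimate moves by −b × s. This is normally less than one-for-one, but not zero.

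**3. The plan's own power figure**

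Inputs from Sample size and power calculation: 15 hospitals × 15 workers, effect size 0.6, ICC 0.06, two-sided 5%, 80% power, and a spread of 6.86. The article calls 6.86 a variance, but its 4.1 points equals 0.6 × 6.86 = 4.116, so it is used as an SD. It is used that way here too, and applied to the change score, whose own SD the article does not give.

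- Allocation 1:1 within strata of 2, 4, 2 and 7 hospitals (6 and 9 per province, 2 coached in each) gives 7 v 8 hospitals, or 105 v 120 workers.
- Design effect: 1 + 14 × 0.06 = 1.84.
- Effective numbers: 105/1.84 = 57.07 and 120/1.84 = 65.22.
- SE in SD units: √(1/57.07 + 1/65.22) = 0.1813.
- Noncentrality at 0.6 SD: 0.6/0.1813 = 3.31.
- Power: about 86% from the noncentral t on 15 − 2 = 13 df, or 91% by the normal approximation. The stated 80% is met as a floor.

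**4. Illustration with assumed shifts**

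Each s below is an assumption, taken to work against a true effect of 4.116 points in the unadjusted analysis with the SE unchanged. The noncentrality is (4.116 − s)/6.86/0.1813.

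| s (points) | Effect estimated on average | In SD | Noncentrality | Power (13 df) |
|---|---|---|---|---|
| 0 | 4.12 | 0.600 | 3.31 | 86% |
| 0.25 | 3.87 | 0.564 | 3.11 | 82% |
| 0.5 | 3.62 | 0.527 | 2.91 | 77% |
| 1 | 3.12 | 0.454 | 2.51 | 64% |
| 1.5 | 2.62 | 0.381 | 2.10 | 50% |

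A shift in the other direction would inflate the estimate. With no true effect, s = 1 gives a noncentrality of 1/6.86/0.1813 = 0.80 and a two-sided type I error of about 12% instead of 5%.

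**The case against.** **Staff may not know their arm when they fill in the form.** This is the strongest point, and it stands as a limit. The article never says when the arm is disclosed, the self-monitoring training is described after the questionnaire, and the trial schedule figure is not shown. A condensed article may also leave disclosure logistics to the full protocol. A reader might infer that the baseline is taken from staff who know their allocation, or who cannot be blinded. The text supports neither: it calls blinding difficult, and only that. But the order of steps is stated in the article itself, and it permits the problem.

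**The size is invented.** In part, yes. No shift of any size or direction follows from the documents, so the table is a sensitivity range and not an estimate. One-for-one bias also holds only for the unadjusted change score. The mechanism itself needs no assumed figure.

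**The knowledge and skills tests are scored instruments.** This stands. Learning one's arm is a weaker threat to a written or simulation test, particularly with assessors unaware of allocation. The concern rests on the questionnaire.

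**The abstract's wording is loose and causes no bias.** This also stands. On the abstract's reading the baseline would precede randomisation, so allocation could not shift it. Coaching comes before randomisation in both arms, and coaching history is a stratification factor, so including the coaching effect changes what the change score contains without favouring an arm. The abstract and the study-entry clock are wording inconsistencies to correct, not sources of the bias.

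**Conclusion.** The concern holds as a design weakness conditional on disclosure. The baseline of the primary change score is self-completed and scheduled after randomisation, in staff for whom blinding is called difficult, and no stated step withholds the allocation until it is complete. If staff learn their arm first, an arm-related shift passes in full into the unadjusted estimate and, scaled by the baseline slope, into the adjusted one.

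A reader might go further and conclude that the primary result will be biased, or will lose a set amount of power. The documents do not support that, because disclosure before baseline is not stated and no shift can be derived. Under the assumptions above, shifts of 0.25 to 1.5 points against a 4.1-point effect would take power from about 86% to between 82% and 50%. The case for acting is that the exposure is avoidable and cannot be repaired in the analysis.

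**What to change.** 1. Complete the post-coaching determinants questionnaire before the hospital's allocation is drawn, or at least before it is disclosed to staff and assessors. For consistency, do the same with the written and simulation tests.
2. Define baseline once, as after coaching and before the allocation is drawn or disclosed. Use that definition in the abstract, Participant timeline, the determinants, knowledge and skills sections, and Data analysis.
3. In Participant timeline, align the one-year period counted from study entry with one year after randomisation.

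**Cost.** A reordering of steps and a wording amendment, with no extra measurements and no change in sample size. The article does not say that randomisation takes place at a hospital visit. If a stratum is randomised together, all its hospitals (up to 7 in the largest) must finish baseline before the allocation is drawn or released, which could delay the first of them. The hospital environment checklist is already scheduled before randomisation, which shows some pre-allocation collection is planned, although testing 15 staff per hospital is more work than a facility checklist.
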